## Discussion

Our feasibility study found unexpectedly high lifetime prevalence for the age group under study: Approximately 12% across products in a sample of predominantly 11 to 12-year-old students. Compared with data from a German national survey of adolescents aged 12 to 13 years^8^, lifetime cigarette use was similar (3.7%), whereas prevalence estimates for disposable e-cigarettes and hookah were higher in our sample (6.5 and 7.6%, respectively). In addition, 36% of never-smokers in our sample were susceptible to future vaping or smoking. This estimate is higher than the recently reported 23% among 12–13 year olds in the United States^55^, and comparable data for Europe are not available.

In addition to our quantitative results, the qualitative findings also suggest that Grade 6 already represents a critical phase of heightened risk and experimentation; accordingly, we chose to target Grade 5 in our intervention. Our participatory research revealed high exposure to vaping and smoking within families, at school and in public settings. The identified barriers and enablers of vaping and smoking largely mirrored established risk and protective factors of smoking initiation identified in previous research^56^. A notable difference, however, was the particular appeal of disposable vapes: their colorful appearance, perceived pleasant smell, and anticipation of appealing flavors appeared to create a strong temptation that even students committed to not smoking described as difficult to resist. In addition, many students expressed substantial uncertainty about the health consequences of vaping. These findings underscore the need for prevention efforts that explicitly address vaping and equip children with the knowledge and skills needed to resist it.

A central aim of the intervention development was to create a program that serves all schools, with a special focus on addressing the needs of schools serving lower-SES-communities. Extensive participatory research with stakeholders, including governmental- and school-level prevention coordinators, school staff and health interventionists working with the target group allowed us to tailor the intervention more closely to the needs of these settings. Although education reports have pointed to the wider strain on school systems^27^, our stakeholder consultations indicated that this strain also translates into limited capacity to implement vaping and smoking prevention in many schools, especially in those serving lower-SES populations. Key barriers included limited staff capacity, the demands of multilingual classrooms, and curricular backlogs that heighten pressure to prioritize core academic subjects. External support, combined with a relatively brief intervention, therefore appears to be the most feasible strategy for ensuring that students in these schools are reached by prevention efforts. The present intervention was designed with these implementation needs in mind.

### Cluster-randomized controlled trial protocol

The primary objective of the trial is to assess the effects of a school-based prevention program with three training sessions on motivation, smoking, and vaping (primary outcome: intention to be vape- and smoke-free across all modes of use) in children in Grade 5 (Age: 10–11 years) at 3, 6, and 12 months after baseline, compared to an active control group receiving the standard curriculum. Smoking and vaping measures include the use of cigarettes, disposable e-cigarettes, reusable e-cigarettes, hookah, tobacco heater, cigars/cigarillos, and pipe.

We will report intervention content based on the well-established Behavior Change Technique Taxonomy^49^ and examine underlying mediators of the program effects. We will recruit students from schools with elevated sociostructural burden and examine risk and protective factors, intervention effects and mechanisms of action in relation to students’ SDOH. The assessment and analysis of both mediating mechanisms and SDOH as moderators are expected to advance a “precision approach” to prevention – bringing us closer to providing the right preventive intervention to the right person at the right time and in the right place^31,57^.

We hypothesize that children in the intervention group, compared with children in the control group, will exhibit

Increased intentions to be vape- and smoke-free (primary endpoint measured at the 12-month follow-up) andDecreased susceptibility to vaping/smoking; vaping/smoking prevalence (lifetime prevalence, 12-month and 30-day prevalence, as well as 30-day-frequency), regular vaping/smoking (≥ once a week), and current vaping/smoking (≥ once a week during the last month).The intervention effects are mediated via 
increased action planning for vaping/smoking refusal; increased vaping/smoking refusal skills (i.e., refusal self-concept and refusal self-efficacy as proxies for actual capabilities); increased self-efficacy to be vape- and smoke-free; increased positive attitudes towards being vape- and smoke-free,increased stress and problem coping (i.e., self-efficacy and planning for coping); and heightened intentions to be vape- and smoke-free (for the outcomes of susceptibility and vaping/smoking behavior only); decreased perceived vaping/smoking norms; decreased negative attitudes towards being vape- and smoke-free.
We will further test hypotheses about differences in risk and protective factors, as well as in vaping/smoking outcomes, by SDOH subgroups (gender, SES, religion/world view, migration history, spoken language, and health status). A detailed description of this examination can be found in our pre-registration file^37^. Additionally, we will explore differential intervention effectiveness as well as underlying mechanisms of change by subgroup.

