### Study aims for the intervention development study and the trial protocol

The aim of this article is twofold: First, we report the participatory development of a school-based prevention program addressing vaping and smoking, tailored to the context of schools serving students from lower socioeconomic backgrounds. Second, we present the protocol for a longitudinal cluster-randomized controlled trial designed to evaluate the program’s effectiveness in strengthening students’ intention to remain nicotine-free and in reducing nicotine initiation and consumption. In addition, the study will examine the mediating mechanisms of program effects to identify which intervention components are critical to the success of vaping and smoking prevention. We will also explore heterogeneity in risk and protective factors, intervention effects, and mechanisms of action according to students’ social determinants of health. The results may therefore provide insights into group-specific needs and inform differentially effective prevention strategies.

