Vaping/smoking behavior in the target group; salient positive and negative beliefs about being vape- and smoke-free, sources of normative influence, and enablers/barriers	The age at which students begin vaping or smoking varied between schools. In our feasibility testing, lifetime prevalence for vaping/smoking was 11.96% (mean age *M* = 11.74, *SD* = 0.70, 53% female) (FEA). In addition, 14.81% of participants were classified as highly susceptible, reporting they would likely or definitely try smoking or vaping. 35.8% were classified as susceptible, indicating they did not rule out the possibility of trying these behaviors (FEA). Regular use was reported from grades 5–6 onward, although it generally involved only 1–2 students per grade cohort (STU, STA, FEA). Students were frequently exposed to vaping/smoking in various environments, including public spaces, family settings (such as through siblings, parents, and cousins) and near school grounds (such as through other students and teachers). Additionally, they were frequently exposed to online content related to e-cigarettes/vaping, often promotional posts created by influencers on social media (TikTok/Twitch/Snapchat, in particular) (STU, STA, FEA). Key barriers to being vape- and smoke-free identified during the student interviews were: Wishing to belong with a group or be cool, being put under pressure or scared or otherwise bullied, being in trouble/stressed and craving stress relief (STU, STA). Key enablers were knowing about health consequences, effects on fitness and potential addiction, family expectations, associated costs, smell, finding smoking unpleasant, and wishing to belong to a group of friends who do not vape and smoke (STU). Students perceived cigarettes as less attractive due to their odor, cost, and negative health effects (STU, FEA). In contrast, disposable e-cigarettes were often perceived as highly attractive due to their sweet flavors, colorful appearance, low cost, and easy accessibility (STU, FEA). Many students who strongly refused to smoke cigarettes found vapes highly tempting (STU). Although most students had at least some knowledge about the health consequences of smoking traditional cigarettes, there was significant uncertainty and doubt about the potential harm of vaping (STU, FEA).	Prevention efforts should begin as early as fifth grade to reach most students before experimentation and susceptibility become more prevalent. The program should place a strong focus on e-cigarette use and prioritize the cultivation of children’s competencies in the following domains: the ability to discern social influences and resist peer pressure, the capacity for critical thinking and the ability to question information encountered on social media, and the development of adaptive coping mechanisms for stress management and problem-solving. Furthermore, the program should foster positive social norms within the peer group that promote vape- and smoke-free living, while communicating the positive outcomes relevant for the target group.

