### Analysis

The analyses on intervention effects will be conducted on an intention-to-treat basis, including data from all students based on the groups they were randomly assigned to. The main confirmatory analysis pertains to the group difference between intervention and control group in intention to be vape- and smokefree at the 12-month follow-up (T4), adjusted for baseline (T0). All other analyses, including analyses of secondary behavioral outcomes and additional time points, will be considered secondary or exploratory, and no formal multiplicity adjustment will be applied.

Group differences in secondary behavioral endpoints (i.e., prevalence and frequency measures) will be analyzed across all product categories (e.g., prevalence defined by the use of at least one of the products presented in the questionnaire) as well as individually for each product reported by at least 1% of the sample.

For continuous and dichotomous outcomes, we will use generalized mixed effect regression analyses (i.e., linear regression for the outcome of intention to be vape- and smoke-free; logistic regression for [binary] susceptibility, prevalence measures, current vaping/smoking and regular vaping/smoking). The primary analyses will use a two-level structure, with students at Level 1 nested within schools at Level 2, reflecting the school-level randomization and the role of the school as the primary clustering unit. In regard to count data, we will use Generalized Estimating Equations to conduct zero-inflated negative binomial regressions for count outcomes with many zeros, i.e., the 30-day frequency. We will investigate intervention effects using the criterion of statistical significance (*p* < 0.05) of the regression coefficients for the treatment condition variable (adjusting for prespecified baseline covariates; all measured at T0: intention, age, gender, parental vaping/smoking, best friend’s vaping/smoking, objective socioeconomic status, school attachment, self-esteem and distress). All models will be specified with a maximal random effects structure and progressively simplified as needed to reach convergence.

To handle missing data appropriately, we will conduct a comprehensive analysis of attrition patterns, multiple imputation and sensitivity analyses to check the robustness of our inferences to departures from the underlying assumption of missingness at random.

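### Reducing initiation is a stated aim, but the nearest endpoint is lifetime prevalence in all pupils without use of their own baseline ever-use; an initiation analysis among baseline never-users should be added

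*Protocol article*

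**What the plan says.** The study aims section of the Protocol article says the trial will evaluate effectiveness in "strengthening students’ intention to remain nicotine-free and in reducing nicotine initiation and consumption".

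The hypotheses in the section Cluster-randomized controlled trial protocol translate the behavioural part into susceptibility, "vaping/smoking prevalence (lifetime prevalence, 12-month and 30-day prevalence, as well as 30-day-frequency", regular use and current use. The Measures section defines the same set, and no outcome is defined as first use among pupils who had not used before.

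Under Analysis, effects are estimated by intention to treat, "including data from all students based on the groups they were randomly assigned to". Binary outcomes get a two-level logistic model. The baseline covariates are "intention, age, gender, parental vaping/smoking, best friend’s vaping/smoking, objective socioeconomic status, school attachment, self-esteem and distress", so parents' and best friend's use are in the list and the pupil's own use is not. Table 4 shows that lifetime prevalence is recorded at T0, T2, T3 and T4. All behavioural outcomes are classed as secondary or exploratory.

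The only figure on prior use comes from the development study. Table 1 reports "In our feasibility testing, lifetime prevalence for vaping/smoking was 11.96" per cent in Grade 6 pupils of mean age 11.74. The trial enrols a grade lower, "in children in Grade 5 (Age: 10–11 years".

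**The concern.** Lifetime use can only go from no to yes. A pupil who tried a product before T0 is counted at T4 whatever the program does, so this group adds the same kind of case to both arms. There are two consequences. The all-pupil odds ratio lies closer to 1 than the odds ratio for new use. And any chance difference between arms in pre-trial use passes straight into the T4 comparison, because nothing in the listed model removes it. A real effect on initiation could be missed, or a pre-trial difference read as a program effect, although T0 data that would prevent both are already collected.

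**Working it through.** **Reproducing the plan's own figure.** The sample size concerns intention. With d = 0.2, two-sided α = 5% (sidedness assumed) and 80% power, n = 393 per arm. The design effect is 1 + 59 × 0.005 = 1.295, giving 509 per arm, or 8.5 schools of 60. With t quantiles on 18 degrees of freedom the need is 9.5, hence 10 schools per arm and 1,200 pupils; 1,200 / 0.80 = 1,500. The stated figures reproduce. The article states no power for any behavioural outcome.

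**Inputs for lifetime prevalence.** From the article: 600 analysed per arm, 60 per school, ICC 0.005 (given for intention, borrowed here), and initiation odds ratios of 0.50 (combined curricula) and 0.88 (all programs) from the review cited in the Introduction. Assumed: control ever-use of 12% at T4, because trial pupils at T4 are about the age of the feasibility sample (11 of 92 = 11.96%); and T0 ever-use b of 2% to 8%, since no Grade 5 value is given.

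**Formulas.**
- Control incidence among T0 never-users: i = (0.12 − b) / (1 − b).
- Intervention incidence i′: apply the odds ratio to i.
- Intervention ever-use at T4, all pupils: b + (1 − b) × i′.
- Effective n per arm: all pupils 600 / 1.295 = 463; never-users 600(1 − b) / [1 + (60(1 − b) − 1) × 0.005].
- Power = Φ[(|p1 − p2| − 1.96 × SE0) / SE1], with SE0 pooled and SE1 unpooled; no gain from covariates is assumed.

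**Worked case, b = 6%, odds ratio 0.50.** i = 0.06 / 0.94 = 0.0638 and i′ = 0.0330. Intervention ever-use at T4 = 0.06 + 0.94 × 0.0330 = 0.0910. The all-pupil odds ratio is (0.0910 / 0.9090) / (0.12 / 0.88) = 0.73.
- All pupils: difference 0.0290, SE0 = SE1 = 0.0202, power Φ(−0.52) = 30%.
- Never-users: n = 564 / 1.277 = 442, difference 0.0309, SE0 = SE1 = 0.0144, power Φ(0.18) = 57%.

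The absolute effect hardly shrinks (3.1 to 2.9 points). Most of the loss is added noise. The chance arm difference in T0 ever-use alone has SD √(2 × 0.06 × 0.94 × 1.295 / 600) = 1.6 points.

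**Results at odds ratio 0.50.**

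| T0 ever-use | All-pupil odds ratio | Power, all pupils | Power, T0 never-users | Ratio |
|---|---|---|---|---|
| 2% | 0.58 | 69% | 78% | 0.88 |
| 4% | 0.65 | 49% | 69% | 0.71 |
| 6% | 0.73 | 30% | 57% | 0.53 |
| 8% | 0.82 | 16% | 42% | 0.37 |

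With ICC 0.02 all powers fall (at 6%: 20% versus 38%) and the ordering is the same. At odds ratio 0.88, power over these T0 values is 4–8% in all pupils and 6–8% in never-users. A simulation with 26 schools of 46 analysed pupils and a school-level t-test agrees at odds ratio 0.50: 65% versus 75%, 48% versus 69% and 31% versus 57% at T0 use of 2%, 4% and 6%.

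**The case against.** The strongest reply is that this is one secondary outcome among several. No behavioural power is claimed, and the all-pupil comparison is a valid randomized test. Twelve-month prevalence at T4 covers roughly the trial year and is not fixed by earlier use. The planned covariates, such as best friend's use, may predict prior use and absorb some imbalance. The Analysis section also foresees alternative codings and longitudinal models and refers to a pre-registration that is not at hand. All of this stands, and it limits the weight of the point. It does not remove it: twelve-month prevalence mixes new with continuing users, and the article itself fixes the endpoint list, the population and the covariates.

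A reader might infer that T0 ever-use cannot be handled as a covariate, because ever-users are all cases and their coefficient has no finite estimate. That does not follow. Only that coefficient diverges; in an ordinary logistic model the treatment estimate stays finite and equals the never-user estimate. In a check on simulated data both gave −0.607 with standard error 0.230.

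One caution applies to the remedy. Table 2 places allocation before T0, and assessment staff know the arm, so T0 never-use is a self-report taken after allocation. T0 precedes the first workshop and pupil briefings are almost identical across arms, which limits the risk without excluding it.

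**Conclusion.** The point holds as a mismatch between aim and endpoint: initiation is named as a target, and the only endpoint near it ignores the pupil's own T0 use. Using T0 ever-use had higher power in every scenario computed.

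A reader might conclude that power is roughly halved. The article does not support that as a general statement. Halving occurs near 6% T0 use when T4 control use is 12%, that is, when about half of T4 ever-users had already used at T0. The loss is about an eighth of the power at 2% and nearly two thirds at 8%. Grade 5 ever-use, 12-month incidence and the program's effect on initiation are all unknown here, and at an odds ratio of 0.88 neither analysis has useful power. Nor does the point touch the primary endpoint, its sample size or the validity of the all-pupil contrast. It warrants an added analysis, not the removal of a registered outcome.

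**What to change.** Add, as the secondary analysis of initiation, first reported use of any listed product by T4 among pupils who reported no lifetime use at T0, with the same two-level logistic model. Nearly equivalently, add T0 ever-use as a covariate in the lifetime-prevalence model. Keep the registered all-pupil lifetime prevalence alongside.

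The cost is one derived variable from data already collected and a few sentences in the hypotheses, Measures and Analysis sections, documented as an update of the pre-registration if it is not already there. The downsides are small: T0 ever-users leave this one analysis, and its population rests on a self-report collected after allocation. Reporting T0 ever-use by arm would let readers judge that.

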### Trial design

A cluster-randomized, controlled, parallel-group, superiority trial will be conducted to investigate the impact of the intervention arm in comparison to an active control arm (standard curriculum taught by the school staff). Intervention lessons and outcome assessments in school will be conducted throughout the school years 2023/24, 2024/25 and 2025/26 in primary schools in Berlin, Germany, that serve Grades 5 and 6 (see Table 2 for the SPIRIT flow diagram schedule of enrolment of schools, interventions, and assessments; see Fig. 2 for the anticipated participant flow). In the German state of Berlin, primary education generally includes Grades 1–6, whereas in most other German states it typically includes Grades 1–4.

**Table 2 Tab2:** Schedule of enrolment, interventions, and assessments.

Timepoint	Study period								
	Enrolment	Allocation	Post-allocation						Close-out
	-t1	0	t0	t1^b^	t2	t3	t4	tn	tn
Enrolment:									
Eligibility screen	X								
Informed consent	X								
Allocation		X							
Interventions:									
Prevention program									
Standard curriculum (active control)									
Assessments:									
Outcomes: intention, susceptibility			X	X	X	X	X	X	X
Outcomes: vaping and smoking behavior			X		X	X	X	X	X
Proposed mechanisms / mediators^a^			X	X	X	X	X	X	X
Program evaluation: students and teachers^b^				X	X	X^c^			
Baseline covariates			X						

T0: Baseline, approximately one week or immediately before the first core workshop, T1: immediately after core workshops 1 and 2, T2: 3 months post-intervention, T3: 6 months post-intervention, T4: 12 months post-intervention, Tn = optional follow-up surveys up to the age of 21. ^a^The following measures are only assessed at T4–T^n^: Affective experience and anxiety (intervention group only), stress and problem coping self-efficacy/planning (intervention and control group). ^b^ measured only in the intervention arm. ^c^  measured in students only.

**Fig. 2 Fig2:**
[figure not shown]
Anticipated participant flow.

The detailed research plan has been registered with the Open Science Framework (25/11/2023)^37^, before the start of baseline data collection, and later with the German Clinical Trials Register, DRKS00036358; 06/03/2025), while recruitment was ongoing. At the time of manuscript submission, recruitment and baseline collection were ongoing. This study protocol and subsequent reports are prepared following the SPIRIT 2013 and CONSORT 2010 statements^58,59^.

### Study population and eligibility criteria

The study will be conducted in the German state and capital of Berlin, an urban area with a smoking prevalence and tobacco-related mortality ranging among the highest of the German states [^76^]. Eligible schools must be located in one of six Berlin districts selected a priori because they rank among the highest in the city in the proportion of students exempt from extra payments for learning materials and/or entitled to the Education and Participation Pass (Bildungs- und Teilhabepaket, BuT) [^77^] These districts are Mitte, Neukölln, Spandau, Reinickendorf, Lichtenberg, and Friedrichshain-Kreuzberg.

To be eligible, schools must be primary or secondary schools that teach both Grades 5 and 6 or, if they normally teach mixed-grade classes, must agree to form grade-specific groups for the duration of the prevention lessons. Although the intervention itself targets Grade 5 students, participating schools also had to teach Grade 6. This requirement was intended to facilitate the 12-month follow-up and reduce attrition due to school transitions between Grades 6 and 7.

Principals will be required to provide written consent to participate in the study, including agreement not to involve any other external vaping or smoking prevention provider, or at least to inform the study team if they do so. In addition, for a school to be included in the study, all classes in the target grade will be required to participate. At the student level, both parents and children will be required to sign consent forms for the data assessment.

